#### Sample size

Previous studies with refugee children show large between-group effect sizes for PTSD symptom severity for KIDNET vs control group and EMDR vs control group [18, 20, 21, 25]. Therefore, at least a medium effect size can be expected when comparing the two treatment conditions (EMDR and KIDNET) to the waitlist control group. With the following assumptions: a correlation between assessments of 0.40, a modest effect size of intervention (ES *f*=0.20), a power of .80, alpha of .05, and two groups (EMDR, KIDNET versus waitlist control group), a total sample of 78 participants will be needed (26 participants per condition), (G*power [49]).

We hypothesized that both interventions (EMDR and KIDNET) are effective in reducing post-traumatic stress symptoms. In case there is a small difference in effectiveness, we aim to detect it. Therefore, the number of participants needed to detect a small effect size (*f*=0.17) is computed, resulting in a preferable sample size of 78 participants (39 participants per treatment condition; EMDR and KIDNET).

After the waitlist period of 8 weeks, the second randomization will take place. Participants will be randomly assigned to EMDR or KIDNET which results in 13 extra participants in both treatments group and thereby a total of 39 participants in both treatment groups. Since a crossover design is not used, the data of the participants (*n*=26) who were secondly randomized into a treatment condition will only be used in the analyses of EMDR versus KIDNET. A conservative 20% attrition rate will be taken into account, resulting in a total required sample of 93 participants.

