### Statistical analyses

Descriptive statistics and analysis of variance will be performed. All three groups will be compared with regard to pre-treatment variables such as demographic variables (age, gender, ethnicity). To test the effectiveness of EMDR vs waitlist control group and KIDNET vs waitlist control group, analyses of variance will be performed with time (T1 and T2) as within-subject variable, and treatment (EMDR, KIDNET, or waitlist control group) as between-subject variable. To test the effectiveness of EMDR compared to KIDNET, analyses of variance will be performed with time (pre-treatment, post-treatment, and follow-up) as within-subject variable, and treatment (EMDR and KIDNET) as between-subject variable. Both analyses will be done twice; with per-protocol sets and intention-to-treat sets. SPSS will be used for multiple imputations techniques for missing data, the per-protocol analyses, and the intention-to-treat analyses. CONSORT criteria will be followed for the statistical analyses (and reporting) of randomized controlled trials. Repeated measures (per session) will be conducted to evaluate treatment progress (CRIES-13 child version).

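### EMDR v KIDNET pools two randomizations, but the stated model has no cohort term: a small, avoidable loss of precision

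*Protocol article*

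**What the plan says.** The Trial design, Waitlist control group and Sample size sections describe two allocation steps. The first assigns children to EMDR, KIDNET or waitlist. The second assigns waitlist children to EMDR or KIDNET: "After the waitlist period of 8 weeks, the second randomization will take place". The Sample size section counts on the second step for numbers, "which results in 13 extra participants in both treatments group and thereby a total of 39 participants in both treatment groups", and uses these children only in the comparison of the two therapies. The planned make-up is therefore 26 + 26 = 52 children from the first randomization and 13 + 13 = 26 from the second.

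The Statistical analyses section specifies the EMDR v KIDNET test as an analysis of variance with three occasions (before treatment, after treatment, follow-up) within subjects and "treatment (EMDR and KIDNET) as between-subject variable". It names no term for the randomization through which a child entered. It also does not say whether the occasion before treatment is T1 or T2 for a waitlist child. The blocked 1:1:1 scheme under Informed consent, randomization, and blinding covers the first step; no scheme is stated for the second.

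**The concern.** The two cohorts differ by design. A first-cohort child's pre-treatment score is the T1 CAPS-CA-5 interview, the same interview that established eligibility, and treatment begins within 4 weeks of it. A waitlist child has passed a further 8 weeks and a T2 assessment, and no new eligibility check is described. If T2 is the starting score, untreated improvement and regression toward the mean fall inside the first cohort's pre-to-post change but largely before the second cohort's. If T1 is the starting score, the waiting period sits inside the second cohort's change. Either way the cohorts can be expected to change by different amounts.

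With treatment as the only between-subject factor, that difference is counted as unexplained variation in the treatment-by-time test. At stake is some precision in a comparison meant to detect a small difference. If the second split happens to be uneven, part of the gap also enters the estimated difference between the therapies.

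**Working it through.** **Inputs.** From the Sample size section: "a correlation between assessments of 0.40", "a power of .80, alpha of .05, and two groups (EMDR, KIDNET versus waitlist control group", "the number of participants needed to detect a small effect size (*f*=0.17) is computed" (the answer given is 78 children, 39 in each therapy) and, for the waitlist comparison at *f* = 0.20, "a total sample of 78 participants will be needed (26 participants per condition". From Table 1: a waitlist effect size of 0.3 in the cited trial of KIDNET against waitlist in refugee children in Germany. The cohort gap *d* (difference in pre-to-post change, in SD units) is not given in the article. I use 0.3 as the reference value and 0.5 to 0.7 as assumptions.

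**Step 1: the plan's own figures.** For the group-by-time test, λ = *f*²·*N*·*m*/(1 − ρ), with *m* occasions and *k* groups, df1 = (*k* − 1)(*m* − 1) and df2 = (*N* − *k*)(*m* − 1).
- *f* = 0.17, *N* = 78, *k* = 2, *m* = 2: λ = 0.0289 × 78 × 2/0.60 = 7.51, power 77.2% (80% needs 84).
- *f* = 0.17, *N* = 78, *k* = 2, *m* = 3: λ = 0.0289 × 78 × 3/0.60 = 11.27, power 85.4% (80% needs 70).
- *f* = 0.20, *k* = 3, *m* = 2: 78 reproduces exactly, power 81.5%. The stated two groups would need 62.

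The 78 at *f* = 0.17 does not reproduce with ρ = 0.40 for either number of occasions. That is a separate matter and does not decide this point.

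**Step 2: what omitting cohort costs.** The second cohort's share is *p* = 26/78 = 1/3, so *p*(1 − *p*) = 2/9. The variance of a change score is 2(1 − 0.40) = 1.20 (SD 1.095). For a pre–post contrast, error variance is multiplied by 1 + (2/9)·*d*²/1.20. Children lost = 78 − 78/multiplier.

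| *d* (SD) | Rise in error variance | Children lost of 78 | Power without cohort | Power with cohort |
|---|---|---|---|---|
| 0.3 | 1.7% | 1.3 | 76.6% | 77.2% |
| 0.5 | 4.6% | 3.5 | 75.4% | 77.2% |
| 0.7 | 9.1% | 6.5 | 73.6% | 77.2% |

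With the three occasions the article specifies, let the cohorts differ only at the first occasion. The multiplier is then 1 + (2/9)·(2/3)*d*²/(2 × 0.60). Power without cohort is 85.0%, 84.3% and 83.2% at *d* = 0.3, 0.5 and 0.7, against 85.4% with it. Simulation of 6,000 trials per setting, run at 0.3 and 0.5, gave 85.6% v 85.9% and 83.7% v 84.8%.

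**Step 3: validity.** With a 13/13 second split, simulated type I error without the cohort term was 5.1%, 4.5% and 4.2% at *d* = 0, 0.5 and 0.8. A constant difference in level between cohorts costs nothing: with a shift of 0.8 SD, power was 85.5% with and without the term. Only a difference in change over time matters.

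**Step 4: an uneven second split.** With 16/10, cohort shares differ by 16/42 − 10/36 = 0.103. The estimate moves by 0.103 × *d*: 0.03 SD at 0.3, and 0.05 to 0.07 SD at 0.5 to 0.7. The shift is equally likely in either direction. If the second step were simple randomization, a split of 16/10 or worse would occur about 33% of the time. Simulated type I error with a 10/16 split was 4.8% at *d* = 0.3 and 5.8% at *d* = 0.8.

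**The case against.** The strongest reply is that nothing here is invalid. Children are allocated at random between EMDR and KIDNET within each cohort, and with the planned 13/13 split cohort is orthogonal to treatment. Leaving out a prognostic factor is then a choice about efficiency, and a condensed article may leave covariates to an analysis plan that is not shown. The first part stands in full. The second stands only in part: the article does not stay silent on the model but writes it out, without the factor that its own design creates.

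Three stronger readings are tempting, and the documents do not support them.
- **Bias.** A reader might infer that pooling biases the therapy comparison. It does not: the shift from an uneven split averages zero over repetitions, and the simulated error rates stay near 5%.
- **Least power to spare.** A reader might infer that this comparison can least afford the loss. With the three occasions specified, it has 85.4% power, against 81.5% for the waitlist comparison in the form that reproduces 78.
- **A large fall.** A reader might apply the 0.40 correlation to a screened population and infer that the first cohort loses 60% of its excess score untreated. With entry above the mean or above +0.5 SD (mean excess 0.80 or 1.14), that gives 0.48 or 0.68 SD. But 0.40 is a planning value for trial participants, and eligibility is a symptom-cluster rule that admits partial PTSD, not a severity cut. If 0.40 is the correlation among selected children, the unselected value would be about 0.59 to 0.64 and the fall 0.33 to 0.41 SD. At the 0.85 retest coefficient that the article gives for the CRIES-13 child version, a different instrument, the fall would be 0.12 to 0.17 SD.

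**Conclusion.** The point holds as a modest loss of precision. At a cohort gap of 0.3 SD, omitting cohort raises error variance by about 1.7%, worth roughly one child of 78 and under one power point. At assumed gaps of 0.5 to 0.7 SD the rise is about 4.6% to 9.1%, worth 3.5 to 6.5 children. It costs 1.9 to 3.6 power points on a two-occasion contrast and 1.1 to 2.2 with three occasions.

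These figures rest on ρ = 0.40, cohort shares of 2:1, and a gap that appears in change over time. Taking 0.3 as the gap assumes that the cited waitlist change is in SD units and carries over to an 8-week wait in this population. The structure is certain from the text; the size is not. Severity is minor, and the change is worth making because it costs almost nothing.

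**What to change.** In the Statistical analyses section, for EMDR v KIDNET:
- Add randomization cohort (first or second) as a between-subject factor, with its interaction with time.
- Define the pre-treatment score as each child's last assessment before treatment: T1 for children allocated to a therapy at the first randomization, T2 for those who waited.
- Optionally report treatment-by-cohort as a descriptive check on pooling, not as a test that decides whether to pool.

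The cost is about one between-subject degree of freedom. The cohort variable already exists and no new data are needed. With no cohort gap, two-occasion power is 77.2% with or without the term, so nothing is lost if the cohorts turn out alike. The change should be fixed before the final assessment, after which the article says the analysts are unblinded.

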#### Informed consent, randomization, and blinding

During the intake, the assessor explains the aim, method, benefits, and potential hazards of the study. The child and his/her legal guardian will then receive the informed consent (also available in Arabic and English). When the child (12 years and older) and his/her legal guardian agree to participate, the assessor obtains informed consent. When a child meets the inclusion criteria, an independent colleague of ARQ Centrum’45 is contacted and uses random allocation software for the random allocation of the participants to EMDR, KIDNET, or the waitlist control group. Random allocation is performed using a randomized block design with variable block sizes and an allocation ratio of 1:1:1. After the allocation is known, the independent colleague will inform the research coordinator. Hereafter, the research coordinator will inform the therapist about the allocation. Neither therapists nor study participants can be blinded to the treatment condition given the nature of the interventions. Independent members of the research team will administer T1–T4 assessments and remain blinded to the two treatment allocations (EMDR and KIDNET). Statistical analyzes will not start until the final assessment has been done. Hereafter, data analysts will no longer be blinded for the treatment allocation.

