## Discussion

As the number of refugees has increased dramatically in the past decade, and half of its population is below the age of 19 years, there is a high need for effective interventions aimed to counteract mental health difficulties. Repeatedly and consistently, refugee children are at increased risk for mental health problems in particular posttraumatic stress (symptoms as well as disorder). Yet negative mental health consequences of experiences with war, violence, and disruption are reluctantly acknowledged and refugees are for several reasons not inclined to seek mental health care, even when this is available. This paper describes a protocol of a randomized controlled trial in refugee children 8–18 years, who reside with at least one caregiver, in the Netherlands. Two trauma-focused interventions are offered at a location close to the living location of the child and his/her caregiver(s). Consort criteria guide the methodology of the study. A total of 93 children of various origins will be recruited for participation. The aim of the study is to determine the efficacy of two evidence-based trauma-focused interventions, KIDNET and EMDR, both compared to a waitlist control group and with each other.

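### The stated total of 93 does not keep 78 participants at the plan's own 20% attrition: it leaves about 74, and power falls slightly, to about 0.79.

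*Protocol article*

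**What the plan says.** The Sample size section makes two calculations and arrives at the same number twice. For the therapies against waitlist, "a total sample of 78 participants will be needed (26 participants per condition"). The inputs given are f = 0.20, a correlation of 0.40 between assessments, and "a power of .80, alpha of .05, and two groups (EMDR, KIDNET versus waitlist control group"). For EMDR against KIDNET the target effect is f = 0.17, "resulting in a preferable sample size of 78 participants (39 participants per treatment condition; EMDR and KIDNET").

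The second 78 is to be reached by re-randomizing the waitlist children after their 8 weeks, "which results in 13 extra participants in both treatments group and thereby a total of 39 participants in both treatment groups".

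The section closes with the attrition step: "A conservative 20% attrition rate will be taken into account, resulting in a total required sample of 93 participants". Trial design carries this through as 31 children in each of three arms, and the Discussion repeats it: "A total of 93 children of various origins will be recruited for participation". Allocation is by a "randomized block design with variable block sizes and an allocation ratio of 1:1:1".

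**The concern.** An attrition allowance should give a number that, after the assumed loss, still leaves the required sample. That means dividing the requirement by the retained proportion. Multiplying by one plus the loss rate gives too few, and 93 looks like the result of that multiplication.

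The statement at stake is the article's main assurance about size: that 93 randomized children protect the 78 on which both power calculations rest, at the attrition rate it names. If the step is wrong, the planned size falls short of 78 for both comparisons at exactly the rate the plan assumes.

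**Working it through.** **Inputs, all from the article.** Required sample 78 (26 per arm, or 39 per therapy); attrition 20%; stated total 93 (31 per arm); f = 0.20, correlation r = 0.40, alpha .05, power .80; for EMDR against KIDNET, f = 0.17.

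**1. Reproduce the base figure of 78.** For a group-by-time interaction with k groups and m times, the noncentrality is lambda = f² x N x m / (1 - r), with (k-1)(m-1) and (N-k)(m-1) degrees of freedom. With k = 3, m = 2, f = 0.20 and r = 0.40, the smallest N that reaches .80 is 76, which becomes 78 in three equal arms. At N = 78, lambda = 0.04 x 78 x 2 / 0.60 = 10.4 on 2 and 75 degrees of freedom, and power is 0.815. The stated 78 is therefore reproduced with three groups.

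**2. Reproduce 93.**
- Multiplying: 78 x 1.2 = 93.6. Per arm, 26 x 1.2 = 31.2, so 31 per arm and 93 in all. This matches.
- Dividing: 78 / 0.80 = 97.5, so 98. Per arm, 26 / 0.80 = 32.5, so 33 per arm and 99 in all. This does not match.

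**3. What 93 delivers at 20% attrition.**
- 93 x 0.80 = 74.4 in total.
- 31 x 0.80 = 24.8 per arm, against 26.
- 74.4 / 2 = 37.2 per therapy, against 39, with the same single 20% loss applied to all 93.
- Largest loss that still keeps 78: (93 - 78) / 93 = 15/93 = 16.1%.
- Shortfall in entrants: 98 - 93 = 5, or 99 - 93 = 6 with equal arms.

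**4. Effect on power, three groups and two times, f = 0.20, r = 0.40.**

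| Completers | Power |
|---|---|
| 78 | 0.815 |
| 76 | 0.804 |
| 75 | 0.798 |
| 74 | 0.792 |

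**5. Effect on power, EMDR against KIDNET, f = 0.17, two groups.** The article does not restate the correlation or the number of measurements for this calculation, so r = 0.40 is assumed and both versions are shown. Statistical analyses describes three time points for this comparison.

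| Completers | Three times | Two times |
|---|---|---|
| 78 | 0.854 | 0.772 |
| 74 | 0.834 | 0.750 |

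**6. Sensitivity scenario only.** Suppose waitlist children lost 20% while waiting and another 20% during treatment and follow-up. Completers for EMDR against KIDNET would then be 62 x 0.8 + 31 x 0.8 x 0.8 = 49.6 + 19.84 = 69.4. At f = 0.17, three times and r = 0.40, power would be 0.807.

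**The case against.** The best defence is that this hardly matters. The minimum for .80 is 76, the shortfall in power at 20% attrition is less than one percentage point below .80, and the effect size, correlation and attrition rate are each far less certain than that. This is right about size and stands. It does not make the three printed figures consistent.

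A second defence is that the analysis does not depend on completers alone. Statistical analyses plans intention-to-treat sets with multiple imputation, and Data collection and management plans the same assessments for children who stop treatment. Counting completers therefore overstates the lost information. That also stands in part. But imputation does not fully restore missing outcomes, the per-protocol analyses do not escape the loss, and the authors themselves chose to inflate for attrition.

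Three stronger readings are tempting, and the document does not support them.
- A reader might infer that waitlist children lose 20% twice, so that the plan really yields about 69 for EMDR against KIDNET. These children do face an additional period in which to leave, but the article gives one attrition rate and does not say it applies to each phase. The plan's own rate gives 74.4.
- A reader might infer that attrition removes 80% power for EMDR against KIDNET. With three time points and r = 0.40, power stays above .80 even at 69.4. With two time points it is already below .80 at 78, so attrition would not be the cause.
- A reader might point to a single therapy against waitlist, where power is 0.733 at 26 per arm and about 0.71 at 24.8. That contrast is below .80 before anyone drops out. Only about two points come from the attrition step; the rest is a separate matter of how many groups the calculation used.

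Finally, calling the allowance conservative describes the assumed rate. Nothing in the article shows that 20% is too low, so the adjective is not an error.

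**Conclusion.** The statement is wrong as written: 78 required, 20% attrition and a total of 93 cannot all hold. No other section repairs it, and attrition is nowhere defined as anything but loss of participants. The conclusion does not depend on how 93 was obtained, since 93 x 0.80 is 74.4 by any route; only the explanation (multiplying by 1.2 and rounding down) is inferred.

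The consequence is small: about four completers, and about two points of power for the three-group test, to just under .80. That power figure rests on the article's f = 0.20 and r = 0.40, with three groups and two times, the setting that reproduces its 78. No test, estimand or planned comparison changes.

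**What to change.** Correct the last sentence of the Sample size section; no extra enrolment is required. Keep 93 and state that:
- it supports 78 completers only up to about 16% attrition;
- at 20% attrition it gives about 74 completers (about 25 per arm, about 37 per therapy), with power of about 0.79 for the three-group, two-time interaction;
- keeping 78 at 20% attrition would take 98, or 99 in three equal arms.

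Optionally, add that waitlist children face an extra period of possible loss before the EMDR against KIDNET comparison, and give about 69 completers as a scenario in which 20% is lost in each phase, labelled as a sensitivity assumption and not as the plan's rate.

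The cost is one revised paragraph and slightly less favourable figures. The 93 in Trial design and in the Discussion can stay.

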### Statistical analyses

Descriptive statistics and analysis of variance will be performed. All three groups will be compared with regard to pre-treatment variables such as demographic variables (age, gender, ethnicity). To test the effectiveness of EMDR vs waitlist control group and KIDNET vs waitlist control group, analyses of variance will be performed with time (T1 and T2) as within-subject variable, and treatment (EMDR, KIDNET, or waitlist control group) as between-subject variable. To test the effectiveness of EMDR compared to KIDNET, analyses of variance will be performed with time (pre-treatment, post-treatment, and follow-up) as within-subject variable, and treatment (EMDR and KIDNET) as between-subject variable. Both analyses will be done twice; with per-protocol sets and intention-to-treat sets. SPSS will be used for multiple imputations techniques for missing data, the per-protocol analyses, and the intention-to-treat analyses. CONSORT criteria will be followed for the statistical analyses (and reporting) of randomized controlled trials. Repeated measures (per session) will be conducted to evaluate treatment progress (CRIES-13 child version).

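### The T1–T2 time-by-treatment ANOVA is a valid change-score test, but adjusting for T1 by ANCOVA would give more precise waitlist comparisons at almost no cost

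*Protocol article*

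**What the plan says.** The Statistical analyses section fixes the model for the waitlist comparisons: "analyses of variance will be performed with time (T1 and T2) as within-subject variable", and "treatment (EMDR, KIDNET, or waitlist control group) as between-subject variable". It names no baseline covariate. EMDR against KIDNET is also tested by analysis of variance, with three times (pre-treatment, post-treatment, follow-up) and two groups.

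The Sample size section assumes "a correlation between assessments of 0.40", an effect size f of 0.20 and "a power of .80, alpha of .05", and arrives at 78 participants, 26 per condition. The waitlist children "who were secondly randomized into a treatment condition will only be used in the analyses of EMDR versus KIDNET", which brings that comparison to 39 per group.

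CAPS-CA-5 severity is measured at T1 in every child (Trial design; Timing of measurements).

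**The concern.** With only T1 and T2, the interaction term asks whether mean change differs between groups. A change score subtracts the whole baseline value, which is too much when the two scores correlate only moderately. ANCOVA subtracts the fraction of baseline that actually predicts T2. The lower the correlation, the more a change score loses, and the plan assumes a low one.

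What is at stake is precision. The trial is small, and the Risks section foresees recruitment difficulties. Information already collected at T1 would be used less well than it could be, and confidence intervals would be wider than necessary.

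**Working it through.** **Inputs from the Sample size section.** r = 0.40, f = 0.20, alpha = 0.05, N = 78, 26 per condition. The three-level factor and the two times come from Statistical analyses. The documents give no SDs, so SDs are an assumption and are varied below.

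**1. Which test was the trial sized on?** For a repeated-measures within-between interaction with k groups and m times:
- λ = f²·N·m/(1−r), df1 = (k−1)(m−1), df2 = (N−k)(m−1).
- With k=3, m=2, N=78: λ = 0.04 × 78 × 2/0.60 = 10.4, df 2 and 75, power 0.815. N=75 gives 0.798, so 78 is the smallest balanced total.
- With k=2, as the text words it, the total would be 62. The between-factor (main effect) version gives 174 with three groups.

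The stated 78 is therefore the three-group, two-time interaction.

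**2. Variance per child, in units of the T2 variance, equal SDs.**
- Change score: 2(1−r) = 2 × 0.60 = 1.20
- T2 alone: 1.00
- ANCOVA on T1: 1−r² = 1−0.16 = 0.84

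ANCOVA/change = 0.84/1.20 = 0.70, a 30% reduction. Confidence intervals narrow by 1−√0.70, about 16%. In general the ratio is (1+r)/2, so the reduction is 35% at r=0.30, 25% at 0.50 and 15% at 0.70.

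**3. Unequal SDs.** Let s = SD(T1)/SD(T2). The change-score variance is s²+1−2rs; ANCOVA stays at 0.84. At r=0.40:

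| s | Change score | T2 alone | ANCOVA | Reduction, ANCOVA v change |
|---|---|---|---|---|
| 1.0 | 1.20 | 1.00 | 0.84 | 30% |
| 0.9 | 1.09 | 1.00 | 0.84 | 23% |
| 0.8 | 1.00 | 1.00 | 0.84 | 16% |
| 0.7 | 0.93 | 1.00 | 0.84 | 10% |
| 0.6 | 0.88 | 1.00 | 0.84 | 5% |

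The change score does worse than T2 alone only when s exceeds 2r = 0.8.

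**4. Power for the waitlist comparisons (equal SDs).**
- Three-group test, N=78: planned λ=10.4, power 0.815. ANCOVA λ = 10.4 × 1.20/0.84 = 14.86, df 2 and 74, power 0.933.
- If both active arms work equally, f=0.20 corresponds to an active–waitlist difference d with 26 × (2/3)d²/1.20 = 10.4, so d = 0.85 SD.
- One active arm v waitlist, 26 per arm: planned noncentrality 0.8485/√(1.20×2/26) = 2.79, df 50, power 0.782. ANCOVA 0.8485/√(0.84×2/26) = 3.34, df 49, power 0.905.

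If the same 0.85 difference (in T2 SDs) is kept and s=0.8, the planned three-group test has power 0.883 against 0.933. The gain shrinks but does not vanish.

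**5. EMDR v KIDNET (three times, 39 v 39).** Assume a constant 0.68 SD difference at post-treatment and follow-up, r=0.40 between all pairs of times and equal SDs.
- Planned 2-df interaction: differences (0, 0.68, 0.68) have a centred sum of squares of 0.68² × 2/3 = 0.308. λ = (39/2) × 0.308/0.60 = 10.0, df 2 and 152, power 0.81.
- ANCOVA on the mean of the two later scores: variance (1+0.40)/2 − 0.40² = 0.70−0.16 = 0.54. Noncentrality 0.68/√(0.54×2/39) = 4.09, df 75, power 0.98.

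**The case against.** The strongest reply is that nothing is broken. Under randomization the interaction test is unbiased, the sample size matches the analysis, and the trial meets its 80% target with the planned test. That stands in full. A reader might infer from the pairwise 0.78 that the plan misses its own target. The documents do not support this, because the trial was sized on the three-group test at 0.815.

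A reader might also conclude flatly that the planned test does worse than discarding baseline. That needs the T1 SD to exceed 0.8 of the T2 SD. Entry requires partial or full PTSD on the CAPS-CA-5, which may narrow the spread at T1, and no SDs are given. The statement is therefore conditional, and so is the 30%.

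The two-time identity does not carry over to EMDR against KIDNET, which has three times, so that comparison needs its own calculation (step 5). Part of the gain there comes from spending one degree of freedom on the average difference instead of two on any pattern. It assumes a difference that is steady over both later times.

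It is tempting to add that pooling the two randomizations without a term for phase inflates variance. Differences in level between the cohorts cancel in a within-subject comparison; only differences in change would matter, and the documents give no basis for assuming any. Nor is there ground to criticise a treatment main effect, since the plan was not sized on one.

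**Conclusion.** The point holds as a matter of efficiency, not validity. For the T1–T2 waitlist comparisons of continuous outcomes, CAPS-CA-5 severity first, ANCOVA has 30% less residual variance than the planned interaction at r=0.40 with equal SDs, 16% less at an SD ratio of 0.8 and 5% less at 0.6. Apart from one degree of freedom, ANCOVA is never less precise than the change score or T2 alone. The power gains in the working rest on equal SDs, on f=0.20 with equally effective active arms, and, for EMDR against KIDNET, on compound symmetry and a constant difference. None of this applies to the binary PTSD-diagnosis outcome. The change is worth making, but the trial would not fail without it.

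**What to change.** In Statistical analyses, replace the T1–T2 repeated-measures ANOVA by an ANCOVA of T2 CAPS-CA-5 severity on treatment (three levels) with T1 severity as covariate, or by a mixed model with a common T1 mean. Report the EMDR–waitlist and KIDNET–waitlist differences, each with a 95% CI. Use the same form for the other continuous outcomes.

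For EMDR against KIDNET, model the post-treatment and follow-up scores with the pre-treatment score as covariate. An indicator for first or second randomization may be added; no gain in precision is claimed for it.

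The cost is one degree of freedom and an edit to the analysis text. No new data are needed, and standard software is enough. The article states that analysis does not begin until the final assessment is done, so the change can be documented before then. The sample size need not change.
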